# STUDY ADVERSE EVENTS

Due to the nature of the intervention, no adverse events are expected that are related to this study. Participants who experience any adverse events related to their circumcision will be expected to seek treatment as per the Kenya national guidelines of male circumcision.

Participants will be reminded not to use mobile phones while driving or riding.

# ETHICAL CONSIDERATIONS

## Informed Consent

All eligible men will be asked to sign and date an informed consent form prior to enrolment. The consent forms shall describe in detail the study procedure in the language the subject is comfortable with (English, Swahili or Dholuo). The subject will be asked to read and review the document. If a subject cannot read, the consent form will be read to them. The study will then be explained to the subject by a study staff, who will also answer any questions that arise. A copy of the informed consent document will be given to the subjects for their records.

## Ethical Approval

All study participants will be fully informed of the study procedures as described above. Ethical approval for this study will be sought from the Kenya Medical Research Institute’s (KEMRI) Ethical Review Committee, the University of Washington’s Human Subjects Division, and the Institutional Review Board at the University of Illinois at Chicago. KEMRI’s review system will involve an initial review of the protocol by the Center for Microbiology Research Scientific Committee. Upon approval, the protocol will be submitted to the KEMRI Scientific Steering Committee to be reviewed for scientific merit. If approved, the protocol will be forwarded to the KEMRI/National Ethics Review Committee for final ethical approval. At the University of Washington, the study proposal will undergo peer review by the International AIDS Research and Training Program before being forwarded to the Human Subjects Division for ethical review.

## Protecting Privacy and Confidentiality

All education, counseling and testing will be done as stipulated in the Kenya national guidelines for safe voluntary medical male circumcision. All participants will be identified using an identification code that will be the same as the client number assigned to them at the clinic. None of the clinic procedures are study procedures. Our study specifically seeks to obtain approval to access client records and to link the data to our study identification number.

All data, including the computer containing the automated SMS software and databases, will be locked in a secure room with access restricted only to authorized study personnel. Similarly, all computers containing study data will be password protected and only accessible to authorized study staff.

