## Potential Risks of Proposed Research to Study Subjects

We anticipate minimal risk to study participants in this study. We do not intend to collect any data about participants’ HIV status. No biological specimen will be collected.

There exists the potential for exposing a participant’s personal information to others, especially if phones are shared. However, the study will not send out any sensitive personal health information. Further, study procedures will be thoroughly explained to participants and they will be consented only if they fully understand study procedures and find the messages acceptable to them. Participants are also allowed to exit from the study at any time.

Patient anonymity may be compromised since the phone numbers to which messages are sent are essentially personal identifiers. However, the computer on which these phone numbers will be stored will be accessible only to specifically designated study staff. Every effort will be made to safeguard subjects from future contact. The electronic databases will not contain participant names. Health information will be protected by coding all information required for the study and keeping the coded data separate from clinic records. The list of coded and uncoded information (linkage sheet) will also be kept separately. This linkage sheet will be maintained for a maximum of five years, after which all links between coded and uncoded data will be broken. All databases will be password protected and accessible only to authorized study staff.

Because we will be accessing clinic records, there is a risk of breach of confidentiality. All study staff will have undergone training in order to ensure that confidentiality of patient data is maximized.

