## Data Storage and Security

All study computers and records will be stored in a secure room with access limited only to authorized staff. All computers and databases will be password-protected with limited access. Daily backup of the data will be done by a designated study staff onto an external hard drive and onto a server at the University of Washington. The external hard drive will be stored in a separate building that houses the data management center for the Research Care and Training Program in Kisumu (Director, [name]).

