# STUDY LIMITATIONS

Due to the nature of the intervention, it will not be possible to blind participants to study group assignment. However, clinicians and nurses involved in the routine care of the participants will be blinded, unless participants disclose to them.

Resumption of sexual intercourse at 42 days will be recorded based on self-reports. Since there is no feasible biological surrogate marker for this measure, our results may be affected by social desirability bias since participants may have a tendency not to report early resumption of sex.

This study will exclude men who do not own or have access to a mobile phone. There may be some selection bias because younger men as well as poor men are less likely to have phones. This may affect the generalizability of results. However, the majority of men in the age-group targeted by the MC intervention already own mobile phones, or have access to one. Furthermore, mobile phone access in general is rapidly expanding, and we expect this not to be a major limitation.

Contamination: It is possible that men in the intervention arm may share messages with friends receiving usual care. However, it is unlikely that such men will be circumcised on the same day.

If participants share phones with others, there exists the potential for exposing personal information to others. However, the study will not send out any sensitive personal health information. Further, study procedures will be thoroughly explained to participants and they will be consented only if they fully understand study procedures and find the messages acceptable to them.

At day 42, recall bias related to resumption of sexual intercourse may also interfere with accuracy of results. However, because the duration of interest is relatively brief, we expect recall to be accurate.

Lost phones or changed phone numbers: Participants will be asked for an alternate phone number, if available. This number would then be used for the final interview should calls to the primary number fail.

Some participants may seek follow-up care at non-participating centers closer to their homes. Participants will be educated to return to the circumcising centers for all follow-up care. Since the clinic number on a patient’s record is a unique identifier across all MC sites operated by the NRHS, patients who seek care at any one of these sites will be identified and their records captured.

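### The study code is the clinic client number, so destroying the linkage sheet breaks no link, and coding gives no protection against anyone who also holds clinic records

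*Protocol*

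**What the plan says.** Section 8.3 (Protecting Privacy and Confidentiality) fixes the identifier: "All participants will be identified using an identification code that will be the same as the client number assigned to them at the clinic". Section 11.0 (Study Limitations) adds that the number on a man's record "is a unique identifier across all MC sites operated by the NRHS".

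Section 8.4 (Potential Risks) describes the protection: "Health information will be protected by coding all information required for the study and keeping the coded data separate from clinic records". It continues: "The list of coded and uncoded information (linkage sheet) will also be kept separately". Then: "This linkage sheet will be maintained for a maximum of five years, after which all links between coded and uncoded data will be broken". It also names a route of harm: "Because we will be accessing clinic records, there is a risk of breach of confidentiality".

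Other sections bear on the point:

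- The schematic in Section 5.2 has an enrolment step in which a study ID is assigned. A later sentence of Section 8.3 speaks of linking client records to the study's own identification number. Both read as if a separate number exists.
- Section 5.2 (Text Message Formulation/Scripting) keeps the clinic number out of the text messages, for confidentiality.
- Section 5.1 (Allocation concealment) has the clinic number written on the allocation envelope, which is then stored.
- Section 6.2 abstracts the client number, mobile number and date of birth from the clinic file.
- Section 9.2 backs the data up daily "onto an external hard drive and onto a server at the University of Washington".
- Section 6.1 has staff tell men, when introducing the study, that study data are anonymous.

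**The concern.** A linkage sheet protects people only if the code in the data means nothing without it. Here the code is the clinic's own number, so every study row carries the key to the man's clinic file. The step presented to the ethics committees as the end of identifiability would then change nothing. Men would have been told their data are anonymous when the identifier points straight to a clinic record. What is at stake is a promise to participants. No estimate or test depends on it.

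**Working it through.** No calculation applies beyond the count of men affected: 600 + 600 = 1,200. The check sets the statements side by side.

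**Step 1: what the linkage sheet does.** Let *c* be the clinic client number and *s* the study code. The sheet maps *s* to *c*. Section 8.3 sets *s* = *c*, so the sheet maps each number to itself and holds nothing that is not already in the row. After it is destroyed, *c* is still in the study data and still on the clinic record. No section removes or replaces *c* in the data when the five years end.

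**Step 2: each safeguard under *s* = *c*.**

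| Safeguard | Effect as written |
| --- | --- |
| Breaking links after at most five years | None, because the identifier is itself the link |
| Linkage sheet kept separately | None, because there is nothing to translate |
| Coding of study data | Fails against anyone who also holds clinic records; to others the client number is only a number |
| Data kept apart from clinic records | Works physically, but a person holding both can rejoin them on the shared number |
| Locked room, passwords, no names, staff training | Unaffected |

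**Step 3: which data become newly exposed.** Age at first sex and number of partners in the last month are abstracted from the clinic file (Section 6.2). So are the day-7 entries on resumption of sex and days since resumption (Section 6.3). A person with NRHS record access can see these already. The study itself generates the baseline questionnaire and the day-42 telephone interview. Section 6.4 makes the interview the source for resumption of sex before day 42, and Section 10.2 plans analyses of time to resumption, number of partners and unprotected sex among men who resumed early. Those answers are the main added exposure.

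**Step 4: how far the key travels.** The number can be looked up across all NRHS circumcision sites (Section 11.0); Section 4 counts 16 fixed and mobile sites in Kisumu East and West. Nothing in Section 9.2 excludes the client number from the daily copies, so it goes with each of them.

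**Step 5: does other text resolve it?** The study-ID step in Section 5.2 and the later sentence in Section 8.3 suggest that a separate number was intended. Neither withdraws the sentence that equates the two, and staff cannot follow both.

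**The case against.** The strongest reply is that this is a drafting slip of limited consequence. The protocol expects minimal risk, stores no names, locks and password-protects its data and trains its staff. Much of the sensitive content already sits in the clinic file. In Section 8.4 the coding text follows the phone-number risk, and the clinic-record risk is answered directly only by training. All of this stands, and it limits the point. It does not remove the contradiction between Sections 8.3 and 8.4, and an intended separate ID still has to be written down.

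A reader might infer more than the protocol supports:

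- **That participants have no protection at all.** Access control, absence of names and training are untouched, and coding and separation fail only against someone holding both sources.
- **That the choice of ID exposes HIV information.** The study does not collect HIV status. Any HIV entry in a clinic file is open to a person with clinic access with or without the study data.
- **That doubt about anonymity will worsen under-reporting of early sex.** Section 11.0 concedes social desirability bias, but nothing ties it to the ID scheme. Men answer by telephone on numbers the study knows, so the interview is not anonymous to them under any scheme.

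Another fair objection is that a new ID alone does not prevent re-identification. Date of birth, date of circumcision and estate of residence are also abstracted, and the envelope bears the clinic number. This is correct, and the fix has to cover it as far as it can.

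**Conclusion.** The point holds as an internal contradiction in participant protection. As written, the promise "after which all links between coded and uncoded data will be broken" cannot be kept, because destroying the sheet leaves every link in place. Against anyone holding both the study data and NRHS records, coding gives no protection. This applies to all 1,200 planned participants, and the added exposure is mainly their baseline and day-42 answers.

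The conclusion assumes that Section 8.3 is followed literally, that the client number stays in the study data, and that the clinic keeps records identifying each man under that number. The protocol says nothing to the contrary. Power, error rates and the treatment effect are unaffected. It should be corrected because it is a stated safeguard that the design does not have, and the correction is cheap.

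**What to change.** Reconcile the schematic in Section 5.2 with Sections 8.3 and 8.4:

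1. At the existing study-ID step, before any data entry and before the envelope is opened, assign an ID unrelated to the client number. The randomisation number will not serve, because the envelope is issued only after the questionnaire and abstraction.
2. Hold the client number only in the linkage file, and the phone number only in the linkage file and the messaging system. Exclude both from the analysis database and its off-site copies.
3. Write the study ID, not the clinic number, on the stored envelope.
4. Replace date of birth with age in the analysis file. Date of circumcision and estate of residence would remain, so some rematching against clinic files cannot be ruled out.
5. Use the linkage file for record abstraction, including day-7 visits made at another NRHS site, so that the first primary outcome is still captured.

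The cost is one extra look-up for the data clerk and small edits to Sections 5.1, 6.2 and 8.3.

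If the client number is kept as the ID, withdraw the linkage-sheet and link-breaking statements in Section 8.4 and the anonymity statement in Section 6.1.

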## Potential Risks of Proposed Research to Study Subjects

We anticipate minimal risk to study participants in this study. We do not intend to collect any data about participants’ HIV status. No biological specimen will be collected.

There exists the potential for exposing a participant’s personal information to others, especially if phones are shared. However, the study will not send out any sensitive personal health information. Further, study procedures will be thoroughly explained to participants and they will be consented only if they fully understand study procedures and find the messages acceptable to them. Participants are also allowed to exit from the study at any time.

Patient anonymity may be compromised since the phone numbers to which messages are sent are essentially personal identifiers. However, the computer on which these phone numbers will be stored will be accessible only to specifically designated study staff. Every effort will be made to safeguard subjects from future contact. The electronic databases will not contain participant names. Health information will be protected by coding all information required for the study and keeping the coded data separate from clinic records. The list of coded and uncoded information (linkage sheet) will also be kept separately. This linkage sheet will be maintained for a maximum of five years, after which all links between coded and uncoded data will be broken. All databases will be password protected and accessible only to authorized study staff.

Because we will be accessing clinic records, there is a risk of breach of confidentiality. All study staff will have undergone training in order to ensure that confidentiality of patient data is maximized.

## Potential Benefits of Proposed Research to Study Subjects and Others

During the administration of the final questionnaire, participants will be invited to visit the clinic should they wish to receive free condoms.

Knowledge gained from this study will help inform policy makers and HIV prevention programs on devising strategies that can improve adherence to the 7-day post-op visit, reduce early resumption of intercourse after MC, and reduce the frequency of unprotected sexual intercourse.

This study will also provide critical information on the feasibility of using mobile telephony-based technology for public health interventions

# DATA COLLECTION AND MANAGEMENT

## Data Collection

Enrollment data will be directly entered into an electronic database as it is collected during the enrollment visit. A study data clerk will be assigned to enter all such data.

All data collected at the 7-day visit will be abstracted from clinic records directly into an electronic database by a study data clerk. Data abstraction for the 7-day visit will be a continuous process and will occur immediately after the expiry of the 7-day post-MC period. We will develop electronic forms that will allow for this process.

For the final follow-up virtual visit (interview at day 42), responses from the questionnaire administered via phone call will be recorded by study staff into an electronic database. If a participant fails to respond to the phone call, study staff will retry twice daily for one week (7 days). If a response is not received by this time, the participant will be considered lost to follow up due to inability to collect data on the final outcome measure. Data entry will be done by designated study staff that will have undergone training.

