## Study Outcome Measures

### Primary Outcome Measures

The primary outcome measure for objective 1 is the proportion of men failing to return for a post-operative clinic visit at 7 days. This proportion will be determined by examining each participant’s clinic records after their 7th post-operative day. Adherence to this clinic visit will be analyzed as a dichotomous variable. Participants will be considered to have ‘attended’ or ‘not attended’ the clinic visit after the elapse of 3 days after the scheduled 7-day visit.

The primary outcome measure for objective 2 is the proportion of men who report resumption of sexual activity before 42 days post-circumcision. This proportion will be determined by self-report using a brief questionnaire delivered via SMS. The analysis will be as a dichotomous variable, with participants considered as having either ‘resumed’ or ‘not resumed.’ Among men who resume sex before 42 days post-circumcision, we will also compare the time to resumption by study arm.

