**Day 7 (+/- 3 day window)**

Abstract data from participant’s clinic records into electronic database

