## Follow-up Visit

According to the Kenya national guidelines for comprehensive male circumcision services [26], circumcised men are required to visit the clinic at 7 days post-procedure. At this visit, the wound is examined for healing progress, signs of infection, and signs of other post-operative surgical complications. Additional examinations and/or referral are done based on the man’s symptoms. All clinic procedures are documented in the patient’s clinic records. These clinical procedures are not study procedures. Our study will only be interested in extracting data from clinic records.

After the 7th post-operative day, study staff will check participants’ clinic records to ascertain their attendance of this visit and to allow for assessment of study outcome measures. A 3-day window before and after the date of the scheduled visit is allowed. Study staff will abstract data from participants’ clinic records. The data collected will include: *date of visit, date of circumcision, type of visit (routine/client-initiated/physician-scheduled), adverse events (event, grade, treatment), resumption of sexual intercourse, days since resumption, and satisfaction with MC procedure*. HIV status and/or test results will NOT be collected as part of this study.

After the scheduled 7-day post-operative visit, participants in the intervention arm will receive one text message on each of the following days post-procedure: days 8, 14, 21, 28, 35, 41 and 42.

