# STATISTICAL CONSIDERATIONS

## Sample Size Justification

We calculated the sample sizes for each specific aim using the methods described by Dupont WD et al. [27] using the following formula:

[figure not shown]

Where
[figure not shown]

n = desired sample size
Zα = standard normal deviate (z-score) corresponding to the 5% significance level (Zα = 1.96)
Zβ = standard normal deviate (z-score) corresponding to the acceptable type II error rate (Zβ = 1.28 for Objective 1; Zβ =0.84 for Objective 2)
p0 = probability of event in controls
p1 = probability of event among participants in the intervention arm, assuming the intervention works as hypothesized
m = number of control subjects per experimental subject

**Objective 1:** To determine the effect of regular, context-sensitive text messages sent to men after undergoing circumcision versus usual care on attendance of the scheduled 7-day post-operative clinic visit. We hypothesize that men who receive the SMS intervention will have higher rates of attendance compared to those receiving usual care.

Assuming that the proportion of men failing to return for the 7-day post-operative visit is 0.57 among the control group ([name], Nyanza Reproductive Health Society: personal communication), and a 2-sided test with a significance level of 0.05, with **600 men in each arm** we will have at least **90% power** to detect a relative risk between the two arms of **0.83** or larger.

**The following table summarizes the range of sample sizes required with different assumptions of the true relative risk of failure to return for subjects in the intervention arm relative to controls:**

|  | RR= 0.5 | RR= 0.6 | RR= 0.7 | RR= 0.8 | **RR = 0.83** | RR= 0.9 |
| --- | --- | --- | --- | --- | --- | --- |
| Sample Size (per arm) **90% power** | 61 | 98 | 177 | 402 | **557** | 1604 |
| Sample Size (per arm) **80% power** | 46 | 74 | 133 | 301 | 416 | 1199 |

**Objective 2:** To determine the proportion of men who resume sexual activity before 42 days post-procedure after receiving regular, context-sensitive text messages versus usual care within the 42 days post-circumcision. We hypothesize that men who receive the SMS intervention will report higher rates of abstinence from sex during the 42 days post-circumcision.

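### Records for the 7-day visit are to be abstracted just after day 7, but the attendance window runs to day 10, so day 8-10 visits could be missed if the record is read only once

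*Protocol*

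**What the plan says.** Four places in the protocol bear on when attendance is read and scored.

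- **Data Collection (9.1)** gives the instruction for the data clerk: "Data abstraction for the 7-day visit will be a continuous process and will occur immediately after the expiry of the 7-day post-MC period".
- **Primary Outcome Measures** says of the proportion failing to return: "This proportion will be determined by examining each participant’s clinic records after their 7th post-operative day". It then gives the scoring rule: "Participants will be considered to have ‘attended’ or ‘not attended’ the clinic visit after the elapse of 3 days after the scheduled 7-day visit".
- **Follow-up Visit (6.3)** says: "After the 7th post-operative day, study staff will check participants’ clinic records to ascertain their attendance of this visit". It adds: "A 3-day window before and after the date of the scheduled visit is allowed". The date of the visit is among the items to be abstracted.
- **The schematic in section 5.2** heads the abstraction step "Day 7 (+/- 3 day window".

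The last three agree that a visit up to day 10 counts. Only Data Collection ties the reading of the record to the end of day 7.

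**The concern.** A record read on about day 8 cannot show a visit that has not yet taken place. If that reading is the only one, a man who attends later but inside the window has no visit on file when he is classified. Waiting until day 10 to classify him does not help if the data were pulled earlier. Clinic records are the only source for this outcome, so nothing else would reveal the error. The same men's other visit data, such as adverse events, would be missed too.

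The loss need not be equal between arms. Only the SMS arm receives messages, daily on days 1-7 and again on day 8, and these could shift when men attend. Informal rechecking is not a safe remedy. The Blinding section names only clinicians and nurses as unaware of assignment, and staff abstracting records are not said to be blinded, so unplanned rechecks could differ by arm.

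**Working it through.** **1. The dates side by side.** The visit is scheduled for day 7. The window runs from 7 - 3 = day 4 to 7 + 3 = day 10. Classification follows once day 10 has passed. Abstraction under Data Collection starts when day 7 has expired, that is, on about day 8. The visits at risk are those on days 8-10.

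**2. The plan's own figure.** Sample Size Justification gives a control failure rate of 0.57 ("Assuming that the proportion of men failing to return for the 7-day post-operative visit is 0.57 among the control group"), relative risk 0.83, two-sided alpha 0.05, 90% power and 1:1 allocation. So p0 = 0.57, p1 = 0.57 × 0.83 = 0.4731, and their mean is p̄ = 0.52155.

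n = [z(α/2)·√(2p̄(1 - p̄)) + z(β)·√(p0(1 - p0) + p1(1 - p1))]² / (p0 - p1)²

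= [1.95996 × 0.70645 + 1.28155 × 0.70312]² / 0.0969² = 5.2244 / 0.0093896 = 556.4, rounded up to **557**.

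This is the stated figure. Solving the same formula for power at 600 per arm gives (0.0969 × √600 - 1.3846) / 0.70312 = 1.4065, or **92.0%**, consistent with the promised minimum of 90%.

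**3. If a single reading just after day 7 were final.** Let f be the share of in-window attenders who come on days 8-10. Each true failure rate p is then recorded as p + f(1 - p). The documents do not give f, so every value below is an assumption. The calculation also treats 0.57 as the failure rate over the full window, which the protocol does not state.

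Example with f = 20% in both arms: control 0.57 + 0.20 × 0.43 = 0.656; SMS 0.4731 + 0.20 × 0.5269 = 0.5785; relative risk 0.882.

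| f, both arms | Control failure | SMS failure | RR | Power, 600 per arm |
|---|---|---|---|---|
| 0% | 0.570 | 0.473 | 0.830 | 92.0% |
| 5% | 0.592 | 0.499 | 0.844 | 89.4% |
| 10% | 0.613 | 0.526 | 0.858 | 86.3% |
| 20% | 0.656 | 0.578 | 0.882 | 79.0% |
| 30% | 0.699 | 0.631 | 0.903 | 70.2% |

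**4. Unequal shares.**

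| f control | f SMS | RR | Chance of a significant result |
|---|---|---|---|
| 10% | 5% | 0.815 | 97.8% |
| 20% | 10% | 0.802 | 99.6% |
| 20% | 15% | 0.842 | 95.8% |
| 10% | 15% | 0.901 | 57.1% |
| 10% | 20% | 0.944 | 22.9% |

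The recorded relative risk stays at 0.83 when f(SMS) × 0.5269 = 0.83 × f(control) × 0.43, that is, when the SMS share is 0.3569 / 0.5269 = 0.68 of the control share. Below that ratio the effect is exaggerated; above it, the effect is diluted.

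**The case against.** A reader might infer that men attending on days 8-10 would be scored as failures. The protocol does not say so. Its only scoring rule classifies men "after the elapse of 3 days after the scheduled 7-day visit", so nobody is due to be scored before the window closes. Data Collection contains no scoring rule and describes abstraction as continuous, which can be read as allowing later updates. The schematic attaches the three-day window to the abstraction step itself. Clinic records carry visit dates, and Study Limitations says that the clinic number identifies a man across all sites of the operating organisation, so a later check could recover a missed visit. Misclassification therefore requires the first reading to be final. This part of the objection stands.

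It does not remove the conflict. With staggered enrolment, continuous more naturally means man by man as each passes day 7, and the same sentence fixes the time. No second reading is described, although the same section sets out repeated attempts for the day-42 call.

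A reader might also infer that the bias must be towards no effect, or that most of the effect would be lost. Neither is supported. Daily messages could bring SMS-arm men in on time, which would leave more late attenders among controls and could exaggerate the effect. The day-8 message might work the other way, but its wording is in Appendix V, which is not in the text reviewed, so nothing shows that it prompts attendance. Large losses of power appear only under particular assumed shares.

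**Conclusion.** The timing conflict is real and concerns a primary outcome. Read literally, Data Collection has the record pulled while up to three days of the window remain open, and valid visits on days 8-10 could then be missed. How many is unknown.

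An equal late share as low as 5% would take power just below the promised 90%, and 30% would take it to 70.2%. With equal shares the relative risk moves towards 1. With unequal shares the direction depends on their ratio: 10% control against 5% SMS gives 0.815, while 10% against 20% gives 0.944. All of these results depend on assumed shares and on a single, final reading of the record.

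The planned 557 and 600 per arm are unaffected. This is a wording conflict to settle before enrolment, not a fault in the design.

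**What to change.** Amend Data Collection so that the final abstraction of 7-day-visit attendance is done on or after day 11, for every participant in both arms. Earlier readings can continue provided that this final one is made for everyone.

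State the attendance rule, a recorded visit on days 4-10, in the same words in Primary Outcome Measures, the section 5.2 schematic, Follow-up Visit and Data Collection.

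The cost is a few edited sentences and a delay of a few days in abstraction. The sample size, the visit schedule and the analysis do not change.
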